# 4. PARTICIPANT SELECTION

## 4.1 Inclusion Criteria

1. Women between 18 and 70 years old;
2. Healthy participants carriers of a germline pathogenic/likely pathogenetic variant (*BRCA1* or *BRCA2* or *PALB2*), **or**

> 5% Tyrer-Cuzick BC risk at 10 years, **or**

with previous diagnosis of intraepithelial neoplasia (surgery for ADH, LCIS, ER positive DCIS) within the last 3 years;

1. Ability to understand and the willingness to sign a written informed consent document.
2. ECOG performance status ≤1 (Karnofsky ≥70%; Appendix B);

5a. For high risk strata: A negative mammogram or any radiological image based on age and center protocol screening within 6 months before baseline visit;

5b. For IEN Strata: A negative mammogram within 12 months before baseline visit

6. A negative transvaginal ultrasound within 6 months before baseline visit.

## 4.2 Exclusion Criteria

1. Diagnosis of ER negative (<10%) DCIS, or history of breast invasive cancer in the previous 5 years;
2. Previous treatment with SERMs or any other hormonal treatment for breast neoplasms;
3. BMI < 18.5 Kg/m^2^ **and/or** Malnutrition Universal Screening Tool (MUST) score ≥2 **and/or** any current or past eating disorders;
4. Any diagnosis of invasive neoplasia, except non-melanoma skin cancer, in the previous 5 years;
5. Any tamoxifen contraindications (abnormal liver function, previous ischemic heart disease, endometrial disorder, previous deep venous thrombosis, history of pulmonary embolus, current or suspected glaucoma, retinopathy and cataract);
6. Current use of warfarin or other anticoagulant drugs
7. Bilateral mastectomy;
8. Pregnancy or desire to become pregnant in the subsequent 9 months after treatment cessation;
9. Diabetes or any other clinical condition that at the investigator’s discretion contraindicates the proposed intervention.
10. No hormonal contraception is allowed during study intervention. Non-hormonal methods will be advised for women of childbearing potential (WOCBP),.

Women must remain abstinent (refrain from heterosexual intercourse) or use non hormonal contraceptive methods with a failure rate of <1% per year during the intervention period and, specifically, from 9 months after the final dose of tamoxifen. A woman is considered to be WOCBP if she is post-menarchal, has not reached a postmenopausal state (>12 continuous months of amenorrhea with no identified cause other than menopause), and is not permanently infertile due to surgery (i.e., removal of ovaries, fallopian tubes, and/or uterus) or other causes determined by the investigator (e.g. Műllerian agenesis). Examples of non-hormonal contraceptive methods with a failure rate of <1% per year include bilateral tubal ligation, male sterilization, and copper intrauterine devices.

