# 5. Interventions and AGENT ADMINISTRATION

## 5.1 Interventions and arms description

Potentially eligible participants will be contacted by a member of the investigator’s team who will explain the study and present lifestyle goals according to national and international recommendations (WCRF. 2018; CREA, 2019 https://www.crea.gov.it/web/alimenti-e-nutrizione/-/linee-guida-per-una-sana-alimentazione-2018). Briefly, WCRF recommendations (WCRF, 2018) specify that individuals should maintain body weight in the normal range, eat vegetables every day, limit daily consumption of energy-dense foods, sugary drinks, red meat, and alcohol, and to be physically active as part of everyday life; to be moderately physically active, equivalent to brisk walking for at least 30 min a day; as fitness improves, to aim for ≥60 min of moderate or ≥30 min of vigorous physical activity every day; and to limit sedentary habits such as watching television, reading a book, playing pc games.

Women expressing their interest in joining the study and after signing the informed consent will be scheduled for baseline visit. After confirming all inclusion and exclusion criteria they will be randomized to one of the following arms:

*Arm 1*

Low dose Tamoxifen (LDT)

Agent: Tamoxifen. Doses: 10 mg every other day

*Arm 2*

Low dose Tamoxifen (LDT) + Intermittent Caloric Restriction (ICR)

Agent: Tamoxifen. Doses: 10 mg every other day

*Arm 3*

Lifestyle intervention (LI) making use of a step counter device

*Arm 4*

Lifestyle intervention (LI) making use of a step counter device + Intermittent Caloric Restriction (ICR).

Duration of intervention: 6 months

*Description of Interventions:*

Low dose Tamoxifen administration

Participants will receive a 7-month drug supply. The participant will be advised to take one tablet (10 mg) every other day (e.g. every odd days) at dinner, always at approximately 8 PM.

Details on treatment administration (e.g., dose and timing) should be noted in the source documents and on the eCRF.

Intermittent Caloric Restriction

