## 7.3 Baseline

Baseline evaluations are:

Fasting glycemia and blood collection for circulating biomarkers; stool sample collection. Date of last menses will be recorded. Physical exam and medical history, vital signs, alcohol and tobacco assessment, anthropometric measurement (height, weight, waist measurement, hip measurement), body composition (BIVA), quality of life assessment; food consumption and level of physical activity enquired through self-administered questionnaires as explained below. Gravindex test will be obtained in women of childbearing potential.

The use of concomitant medications and any baseline symptom will be recorded.

At baseline, participants will be instructed about the importance of drug compliance, and lifestyle recommendation/instruction based on the randomization arm.

Participants will be provided and instructed on how to fill-up the calendar that will be dated and signed.

Participants will be informed that a pill count will be conducted on their study medication use so that their study medication blisters with remaining tablets must be returned at the clinic visit.

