## 10.2 Serious Adverse Events

Definition of SAE

Serious adverse event (SAE) is defined as one of the following:

Is fatal or life-threatening

Results in persistent or significant disability/incapacity

Constitutes a congenital anomaly/birth defect

Is medically significant, i.e., defined as an event that jeopardizes the patient or may require medical or surgical intervention to prevent one of the outcomes listed above

Requires inpatient hospitalization or prolongation of existing hospitalization.

Note that hospitalizations for the following reasons should not be reported as serious adverse events:

Routine treatment or monitoring of the studied indication, not associated with any deterioration in condition (i.e. to perform study related assessments)

Elective or pre-planned treatment for a pre-existing condition that is unrelated to the indication under study and has not worsened since signing the informed consent

Social reasons and respite care in the absence of any deterioration in the patient’s general condition

Note that treatment on an emergency outpatient basis that does not result in hospital admission and involves an event not fulfilling any of the definitions of a SAE given above is not a serious adverse event

Reporting

To ensure patient safety every SAE, regardless of suspected causality, occurring after the patient has provided informed consent and until at least 30 days after the patient has stopped study treatment must be reported to the EIO Pharmacy within 24 hours of learning of its occurrence.

Any additional information for the SAE including complications, progression of the initial SAE, and recurrent episodes must be reported as follow-up to the original episode within 24 hours of the investigator receiving the follow-up information. A SAE occurring at a different time interval or otherwise considered completely unrelated to a previously reported one should be reported separately as a new event.

Any SAEs experienced after the 30-day safety evaluation follow-up period should only be reported to the EIO Pharmacy if the investigator suspects a causal relationship to the study treatment.

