Information about all SAEs is collected and recorded on the Adverse Event Report Form; all applicable sections of the form must be completed to provide a clinically thorough report. The Investigator must assess and record the relationship of each SAE to each specific study treatment (if there is more than one study treatment), complete the AE Report Form in English, and submit the completed form within 24 hours to EIO Pharmacy.

Follow-up information is submitted in the same way as the original AE Report. Each reoccurrence, complication, or progression of the original event should be reported as a follow-up to that event regardless of when it occurs. The follow-up information should describe whether the event has resolved or continues, if and how it was treated, whether the blind was broken or not (if applicable), and whether the patient continued or withdrew from study participation.

If the SAE is not previously documented in the Investigator’s Brochure or Drug Package Insert (new occurrence) and is thought to be related to the study treatment, the Safety Committee of EIO may urgently require further information from the investigator for Health Authority reporting. Suspected Unexpected Serious Adverse Reactions (SUSARs) will be collected and reported to the Competent Authorities and relevant Ethics Committees in accordance with applicable national regulatory requirements.

Pregnancies

Should pregnancy occur, to ensure patient safety, each event must be reported to the EIO Pharmacy within 24 hours of learning of its occurrence.

The pregnancy should be followed up to determine outcome, including spontaneous or voluntary termination, details of the birth, and the presence or absence of any birth defects, congenital abnormalities, or maternal and/or newborn complications.

Pregnancy follow-up should be recorded on the same form and should include an assessment of the possible relationship to the study treatment any pregnancy outcome. Any AE experienced during pregnancy must be reported on the AE Report Form.

The Study Doctor will collect information such as progression of the pregnancy, the pregnancy outcome and the health of the baby. The collection of this information could last for up to 3 months following the birth of the child, and longer if required by the Safety Committee. Consent to report information regarding these pregnancy outcomes should be obtained from the mother.

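### Section 4.2 starts the post-treatment contraception duty nine months after the last tamoxifen dose, where it should end it

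*Protocol*

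**What the plan says.** Section 4.2 of the protocol sets out the contraception rule after the numbered exclusion criteria. Women must abstain from heterosexual intercourse or use a non-hormonal method failing in under 1% of users a year, "during the intervention period and, specifically, from 9 months after the final dose of tamoxifen".

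Two numbered exclusions in the same section bear on it. Exclusion 8 rules out "Pregnancy or desire to become pregnant in the subsequent 9 months after treatment cessation". Exclusion 10 says "No hormonal contraception is allowed during study intervention", which concerns the treatment period only.

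Other parts of the protocol touch on pregnancy or on post-treatment safety:

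- Section 5.1: "Duration of intervention: 6 months".
- Section 7.3, on testing at baseline: "Gravindex test will be obtained in women of childbearing potential".
- Section 7.7 lists a positive pregnancy test among the reasons for stopping the intervention.
- Section 10.2, on pregnancies that occur: "each event must be reported to the EIO Pharmacy within 24 hours of learning of its occurrence".
- Section 10.2, on the window for serious adverse events: "until at least 30 days after the patient has stopped study treatment must be reported".

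**The concern.** A duty that runs *from* a date begins on that date. The sentence therefore gives two periods: the intervention itself, and an open-ended period that begins nine months after the last dose. The interval between them, when exclusion 8 says no pregnancy should be planned, is left out.

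The sentence is not background. Staff at four centres have to apply it and pass it on to participants. Eligible women are aged 18 to 70 and include carriers of germline variants, and the protocol expects some participants to be too young for mammography, so women of childbearing potential will be enrolled. Section 2.3 itself notes that tamoxifen has a long half-life, which supports a protected period after the last dose. At stake is whether a woman who has finished tamoxifen is told that she still needs contraception.

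**Working it through.** No power or sample-size calculation applies. The check is a timeline and a search of the protocol for any other statement of the duty.

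**Inputs**

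- Intervention: 6 months (section 5.1), so the last dose is taken at about month 6.
- Post-treatment period: 9 months (section 4.2, exclusion 8).
- End of that period: 6 + 9 = month 15.

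**Timeline**

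| Months from randomization | Exclusion 8: no planned pregnancy | 4.2 duty as written | 4.2 duty with *until* |
| --- | --- | --- | --- |
| 0 to 6 (treatment) | not the period it names | yes | yes |
| 6 to 15 | yes | no | yes |
| after 15 | no | yes, without end | no |

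As written, the rule covers 0 of the 9 months named in exclusion 8 and then applies indefinitely. With *until*, it runs without a break from month 0 to month 15 and covers 9 of 9.

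**Does anything else supply the rule?**

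- Exclusion 8 screens pregnancy and intention at entry. It imposes no contraceptive duty after dosing.
- Exclusion 10 restricts the type of contraception during the intervention and gives no post-dose period.
- The schedule of events (section 7.1) has seven time points, T0 to T6. A pregnancy test is scheduled at one of them, T1.
- Tamoxifen safety is reviewed in Arms 1 and 2 at five of them, T2 to T6. The schedule does not name contraception as part of that review.
- The last scheduled contact is T6, at 6 months. No study visit falls inside months 6 to 15.
- Section 7.7 provides for a pregnancy found on treatment, and section 10.2 for reporting one once it is known. Neither tells a woman how long to avoid pregnancy.

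The window for serious adverse events in section 10.2 is also counted from the end of treatment, and there the protocol uses *until*. That supports reading *from* in section 4.2 as a slip.

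**The case against.** The strongest reply is that nobody would be misled. Contraception on treatment, none for nine months, then contraception for ever is absurd, and exclusion 8 a few lines above supplies the only sensible meaning. Strictly, the two clauses do not exclude each other: one concerns eligibility, the other conduct, and a woman could satisfy both as written. Participants also act on the consent form and on counselling. Neither the consent form nor the Summary of Product Characteristics could be consulted. The three example methods (tubal ligation, male sterilization, copper device) ordinarily continue after the last dose, so the practical gap falls mainly on women relying on abstinence. Sample size, randomization and the SHBG analysis are untouched.

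Most of this stands, and it limits the weight of the point. It is a drafting error, not a flaw in the design, and its practical effect is probably small. It does not make the sentence correct. A safety instruction should not have to be repaired by inference from an entry criterion, and nothing else in the protocol as supplied states the duty.

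Two further remarks are fair. The sentence names no arm, although Arms 3 and 4 have no last tamoxifen dose. And once corrected, it would call for abstinence or non-hormonal methods for nine months after treatment, whereas exclusion 10 bars hormonal methods only during the intervention. Both merit clarification while the sentence is being edited; neither makes the correction unsound.

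**Conclusion.** The concern holds. As written, section 4.2 leaves uncovered all 9 of the months that exclusion 8 identifies and then imposes a duty with no end date. The nine-month period itself is sound; only the wording is wrong.

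The number of women exposed cannot be calculated, because the protocol gives neither the share of childbearing potential nor the methods in use. It is probably small and mainly concerns women in Arms 1 and 2 who rely on abstinence; that is a judgement, not a figure from the document. The timeline assumes a last dose at about month 6. A woman who stops earlier has the same nine-month gap, starting sooner. Whether participants were in fact told the wrong period cannot be settled without the consent form. The correction should be made because this is operative safety text.

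**What to change.** In section 4.2, replace *from* with *until*, so that the duty runs through the intervention and up to nine months after the last tamoxifen dose. This agrees with exclusion 8 and with the way section 10.2 words its own post-treatment window. Check that the consent form gives the same period.

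In the same edit it would be sensible to say that the post-dose period applies to Arms 1 and 2, and whether hormonal methods are allowed once the intervention has ended.

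The cost is one word, plus any optional clarification, and a check of the consent form. Visits, sample size and analysis do not change.

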# 5. Interventions and AGENT ADMINISTRATION

## 5.1 Interventions and arms description

Potentially eligible participants will be contacted by a member of the investigator’s team who will explain the study and present lifestyle goals according to national and international recommendations (WCRF. 2018; CREA, 2019 https://www.crea.gov.it/web/alimenti-e-nutrizione/-/linee-guida-per-una-sana-alimentazione-2018). Briefly, WCRF recommendations (WCRF, 2018) specify that individuals should maintain body weight in the normal range, eat vegetables every day, limit daily consumption of energy-dense foods, sugary drinks, red meat, and alcohol, and to be physically active as part of everyday life; to be moderately physically active, equivalent to brisk walking for at least 30 min a day; as fitness improves, to aim for ≥60 min of moderate or ≥30 min of vigorous physical activity every day; and to limit sedentary habits such as watching television, reading a book, playing pc games.

Women expressing their interest in joining the study and after signing the informed consent will be scheduled for baseline visit. After confirming all inclusion and exclusion criteria they will be randomized to one of the following arms:

*Arm 1*

Low dose Tamoxifen (LDT)

Agent: Tamoxifen. Doses: 10 mg every other day

*Arm 2*

Low dose Tamoxifen (LDT) + Intermittent Caloric Restriction (ICR)

Agent: Tamoxifen. Doses: 10 mg every other day

*Arm 3*

Lifestyle intervention (LI) making use of a step counter device

*Arm 4*

Lifestyle intervention (LI) making use of a step counter device + Intermittent Caloric Restriction (ICR).

Duration of intervention: 6 months

*Description of Interventions:*

Low dose Tamoxifen administration

Participants will receive a 7-month drug supply. The participant will be advised to take one tablet (10 mg) every other day (e.g. every odd days) at dinner, always at approximately 8 PM.

Details on treatment administration (e.g., dose and timing) should be noted in the source documents and on the eCRF.

Intermittent Caloric Restriction

We will propose the so-called “5:2 diet,” with 5 days/week at regular energy intake and 2 days/week at an ∼75% energy deficit (the diet will be restricted at 500-700 Kcal per day, corresponding to a 75% reduction compared to normal intake). Detailed personalized meal plans will be created for each participant, in which portion sizes are reported and possible choices for meal components arranged by food groups to meet the target caloric amount foresee. Participants will receive a leaflet containing dietary advice and physical activity recommendations to be followed for the study period. During the 2 days of energy restriction, a daily intake of a minimum of 2 L of liquids (water, tea or infusions) will be strongly recommended to avoid dehydration and side effects of fasting such as hunger and lightheadedness, increased cold sensitivity, weakness and headaches. Trained dietitians/nutritionists will provide personal nutrition consultations at baseline and during the study period. The intervention will be monitored and reinforced by phone call at month 1, 2 and 5, and to monitor possible side effects. The first personal consultation within the first month will be used to motivate participants, to monitor compliance, and to consolidate knowledge about dietary programs proposed. Participants will be instructed to complete a fasting diary to monitor the frequency of energy-restricted days. During the 2 days of ICR, women will be advised to avoid tiring and particularly intense activities. If women are used to practice sport, it will be suggested to walk or practice yoga, meditation and light pilates sessions.

Lifestyle intervention

Participants will receive personalized advice on healthy lifestyle and the use of a step counter device. These devices tend to encourage both increased physical activity and decreased sedentary time. They are able to record total steps taken, total distance traveled, total time active during the day and the greatest length of time of consistent movements done during the day. A goal of "10.000 steps" per day has been widely promoted and advocated as a strategy for increasing physical activity among able adults. Participants will be asked to wear the step counter during the 6-month intervention period. They could use a smartphone or a tablet application to get feedback on their activity and sedentary time.

Training sessions for nutritionists/dietitians involved in the intervention (lifestyle and caloric restriction) will be organized by IEO as a coordinating center, in order to standardize nutritional counseling and interventions.

## 5.2 Contraindications

Eligible participants should not have specific contraindication to tamoxifen, considering also the short period of treatment. Any pre-existing condition that may impact on participant quality of life should be carefully evaluated before enrolling the participants. Furthermore, medications that may impact participant safety or scientific integrity of the study are non-allowed, such as strong CYP 2D6 inhibitors (*e.g*., paroxetine, fluoxetine or St. John’s wort).

Women with documented history of diabetes, current or past eating disorders, uncontrolled intercurrent illness will be excluded.

## 5.3 Concomitant Medications

All medications (prescription and over-the-counter), vitamin and mineral supplements, and/or herbs taken by the participant will be documented on the concomitant medication CRF and will include: 1) start and stop date, dose and route of administration, and indication. Medications taken for medical procedure (*e.g*., biopsy) should also be included.

##

## 5.3.1 Permitted and prohibited medications

The use of tamoxifen in patients receiving dicumarol-type anticoagulant therapy may significantly increase anticoagulant activity; this association must be avoided.

Tamoxifen combination with cytotoxic drugs may increase risk of thromboembolic events episodes this association must be avoided.

Tamoxifen metabolism uses mainly the CYP3A4 and CYP2D6 enzyme. Concomitant medications that interact with these enzymes may result in reduced tamoxifen efficacy. In particular, the combination of tamoxifen and certain SSRI antidepressants or other inhibitor of CYP2D6 (e.g., paroxetine, fluoxetine, quinidine, cinacalcet, or bupropion) should be avoided, since a reduction of tamoxifen efficacy cannot be excluded.

Potentially, any other drug is permitted: participants can take over-the-counter drugs; for drugs prescriptions, participants are asked to inform the investigational staff before treatment initiation.

